### Study Population

#### Sample Size Estimation

Given the focus of this study on the acceptability and feasibility, rather than the efficacy, of the MI-Coach: ED app, formal analytic methods were not used to estimate the prehoc sample size. In keeping with previous feasibility studies in the ED field [14,33,34] and pilot study guidelines, which suggest that modest sample sizes based on the pragmatics of recruitment are sufficient when evaluating the processes, feasibility, and preliminary acceptability of novel interventions [32,35], a sample size of 30 participants was selected, recruited while they wait for ED services and treatments in British Columbia, Canada. Additionally, it was determined that qualitative interviews would be conducted with interested participants on a rolling basis until thematic saturation is reached [36].

#### Participant Recruitment

ED treatment providers and clinicians located in British Columbia were contacted by email and asked to distribute study recruitment flyers providing an overview of the study, incentives, and instructions to contact the study team to indicate their interest to clients on their waitlists (Multimedia Appendix 1). To address existing barriers to ED treatment (eg, logistical challenges and clinician burnout [6,37]) and research [38], a multipronged approach to recruitment has been used in previous studies [15,39], whereby clinician-based referrals are supplemented by web-based recruitment and partnerships with peer support organizations. As such, clinician-based referrals were supplemented by web-based recruitment strategies, including postings on the National Eating Disorder Information Center website and social media, as well as partnerships with peer support organizations. Additionally, a research partnership was established with a local provincial health authority, the Vancouver Coastal Health Eating Disorders Program, which embedded the study flyer as part of an initial resource package provided to patients newly added to their waitlist. Given the findings that recruitment strategies influence sample characteristics and engagement [38], this multipronged approach aimed to maximize the accessibility of the study and diversity within the study sample.

#### Eligibility Criteria

Eligibility criteria were (1) being on a waitlist to receive services for an ED-specific concern and not for a separate mental disorder in British Columbia, (2) being at least 18 years of age, (3) self-identifying as a woman, (4) fluency in written and spoken English, (5) meeting the criteria for a diagnosis of a threshold or subthreshold ED (ie, BN, AN-R, AN-BP, BED, and OSFED), (6) absence of psychosis or diagnosis of a schizophrenia-spectrum disorder, and (7) absence of cognitive impairments or sensory deficits that may interfere with technology use (eg, hearing impairments and recent traumatic brain injury).

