### Outcomes and Measures

The primary outcomes that will be evaluated are the overall acceptability and feasibility of the MI-Coach: ED (Multimedia Appendix 3)*.* Feasibility will be assessed through attrition rates throughout the study period, frequency of app use, and module completion. Acceptability will be assessed through qualitative and quantitative feedback from participants through semistructured interviews and self-reports. Additionally, exploratory analyses will be conducted regarding the impacts of the MI-Coach: ED app on motivation and associated clinical characteristics.

Self-reported demographic data, including gender identity, age, level of education, ethnicity, and socioeconomic status were collected using Qualtrics, a web-based and secure data collection platform. Additionally, clinical data (ie, weight and height, history of ED treatment, age of ED onset, presence of cognitive difficulties, sensory deficits, history of traumatic brain injury, other mental health comorbidities, and ED waitlist experiences) was collected. The Sick, Control, One, Fat, and Food questionnaire [43], a brief screener that identifies the presence of common ED symptoms, was used to determine eligibility prior to enrollment. Clinical characteristics (ie, eating pathology, recovery motivation, body dissatisfaction, depression, and anxiety symptoms) were evaluated through several self-report questionnaires administered at baseline and posttest, including the Eating Disorder Examination Questionnaire (EDE-Q) [44], the Readiness and Motivation for Change Questionnaire (RMQ) [45], the Body Shape Questionnaire (BSQ) [46], the Patient Health Questionnaire-9 (PHQ-9) [47], and the 7-item General Anxiety Disorder Scale (GAD-7) [48]. Additionally, technological literacy was evaluated at baseline using the Mobile Device Proficiency Questionnaire [49] and the eHealth Literacy Scale [50].

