Quantitative measures of feasibility and acceptability of the MI-Coach: ED app were assessed using an adapted version of the TAM Questionnaire [31] and the user version of the Mobile App Rating Scale (uMARS) [51]. The adapted version of the TAM questionnaire includes changes to each item to better fit the research question and sample characteristics of this study (eg, “Using CHART-MASTER in my job would enable me to accomplish tasks more quickly” was modified to “Using MI-Coach: ED allowed me to access mental health services more quickly”). An optional semistructured interview was conducted with interested participants to assess their experiences with the app and to further evaluate the feasibility and acceptability of MI-Coach: ED.

An overview of participant flow is provided in Figure 2. Participants were recruited between November 2022 and April 2024. Clinicians and administrators working in a range of ED treatment settings (eg, provincial health authorities, nonprofit charities, and private practice clinics) were contacted via email and asked to share the recruitment advertisement with clients on their waitlists. Interested participants were asked to communicate with the study team via email to enroll in the study. Once initial contact was established, a 15-minute telephone screener was conducted by the study team to assess participants’ eligibility for the study and to provide additional details regarding the study. The Sick, Control, One, Fat, and Food questionnaire was used to evaluate the presence of ED symptoms. Once eligibility was established, consent (Multimedia Appendix 4) and baseline measures were collected through Qualtrics, including a demographics questionnaire, the EDE-Q, the RMQ, the PHQ-9, the GAD-7, and the BSQ. Following this, an onboarding session was conducted through a secure videoconferencing platform (ie, Zoom), during which participants were given a demonstration on downloading and using the app and provided their log-in information.

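### Eligibility requires meeting eating-disorder diagnostic criteria, but the only eating-disorder eligibility tool stated is a brief symptom screener

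*Protocol article*

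**What the plan says.** In the protocol article, Eligibility Criteria, the fifth criterion is "meeting the criteria for a diagnosis of a threshold or subthreshold ED", with BN, AN-R, AN-BP, BED and OSFED listed as the categories. The first criterion separately requires a place on a British Columbia waitlist for an ED-specific concern.

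Outcomes and Measures says how ED eligibility was decided. The Sick, Control, One, Fat, and Food questionnaire is "a brief screener that identifies the presence of common ED symptoms, was used to determine eligibility prior to enrollment". The enrolment account in the same section says that "a 15-minute telephone screener was conducted by the study team to assess" eligibility, and then that "The Sick, Control, One, Fat, and Food questionnaire was used to evaluate the presence of ED symptoms".

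The order of events is given: "Once eligibility was established, consent (Multimedia Appendix 4) and baseline measures were collected through Qualtrics". The EDE-Q is among those baseline measures. Its stated role is to describe clinical characteristics, which "were evaluated through several self-report questionnaires administered at baseline and posttest".

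Under Participant Recruitment, "clinician-based referrals were supplemented by web-based recruitment strategies", together with peer-support partnerships. Statistical Analysis counts a participant as reliably improved only if the change is reliable and the score has moved out of the clinical range.

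**The concern.** The article names both a criterion and the tool used to decide it, and the two do not match. The criterion concerns diagnostic criteria and specific categories. The tool, in the article's own description, concerns the presence of common symptoms. This is therefore a disagreement between two stated things, and not a detail left to a fuller document.

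Two things are at stake. The first is whom the results describe. The Conclusions say that recruitment, retention and engagement data will shape later large-scale efficacy evaluations, and that exploratory results will supply effect sizes for a randomised trial's power calculation. Planners of that trial need to know whether the pilot population met diagnostic criteria or was waitlisted and screen-positive.

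The second is the clinical-significance analysis. Neither a symptom screen nor subthreshold status ensures that a participant starts above the clinical cutoff, yet the improvement category can be reached only from above it.

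**Working it through.** The plan has no figure to reproduce. The sample size of 30 was chosen pragmatically, and the mismatch does not depend on it. The check is a comparison of the stated texts, followed by one piece of arithmetic on the denominator.

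**1. What the criterion needs against what the tool gives**

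| Question | Criterion 5 (Eligibility Criteria) | Screener (Outcomes and Measures) |
|---|---|---|
| Are diagnostic criteria met, at threshold or subthreshold level? | Required | Described as detecting common symptoms only |
| Which of BN, AN-R, AN-BP, BED or OSFED? | Categories listed | No ability to separate them is described |
| When is it decided? | At entry | At entry, around the telephone call |

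**2. Does anything else stated fill the gap?**

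- *EDE-Q:* collected after eligibility was established, so it did not decide entry.
- *Clinician confirmation:* none is described. Clinicians were asked to pass on study flyers, and interested people contacted the study team themselves.
- *Waitlist criterion:* requires a place on the list for an ED-specific concern. It makes an ED likely but does not itself require that diagnostic criteria be met.
- *Clinical data list:* includes treatment history, age of onset and comorbidities, but no ED diagnosis.
- *Diagnostic interview, chart check or subtype algorithm:* none is stated.

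So, as described, criterion 5 is verified only to the level of symptoms being present.

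**3. How many participants might not meet criteria?**

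This would need the screener's positive predictive value among women on ED waitlists. The article gives no cutoff, sensitivity, specificity or prevalence, so the number cannot be derived.

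**4. Effect on the improvement category**

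Let n be the number analysed and k the number below the clinical cutoff at baseline. A participant below the cutoff at the start cannot cease to meet it, so the largest attainable proportion reliably improved is (n − k)/n. Taking n = 30 (the planned sample, assuming that all complete the posttest):

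- each such participant lowers the ceiling by 1/30 = 3.3 percentage points;
- k = 3 gives (30 − 3)/30 = 27/30 = 90%;
- k = 6 gives (30 − 6)/30 = 24/30 = 80%.

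The values of k are illustrative assumptions. The true k for each measure can be counted from the baseline data.

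**The case against.** The strongest reply is that the article is condensed. The telephone script and the appendix on measures are not shown, and the symptom questionnaire may have been only one part of the call. This stands in part. It is why the conclusion is conditional on no other method having been used. It does not remove the mismatch, because the article itself says which tool determined eligibility.

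A second reply is that the criterion asks for criteria to be met, at threshold or subthreshold level, and does not ask for a formal diagnosis. No planned analysis uses diagnostic subtype, and elsewhere the article describes its participants as women or individuals on ED waitlists. This also stands, and it limits the consequence to description, generalisability and the exploratory clinical results.

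A reader might go further in four ways that the documents do not support:

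- *Web recruits had no clinician behind them.* The article does not say so. Every participant, by any route, had to be on an ED waitlist, and seeing a web posting says nothing about how she came to be on it.
- *Height and weight were collected only after eligibility was decided.* Their timing is not given. They are listed with items that bear on eligibility, such as cognitive difficulties and sensory deficits.
- *A particular number of the 30 are not cases.* Any such figure needs a predictive value that the article does not supply.
- *A baseline score below the cutoff marks a non-case.* Subthreshold disorder is admitted by design, so perfect diagnostic verification could still leave some participants below it.

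**Conclusion.** The point holds as a stated mismatch between criterion 5 and the tool that decided it. As described, the study can show that participants were on an ED waitlist and, assuming that a positive screen was required for entry, screen-positive. It cannot show that diagnostic criteria were met or which category applied.

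The size is unknown and may be small, given the waitlist requirement and the admission of subthreshold disorder. A reader might infer that the sample is largely undiagnosed or contaminated by non-cases. The documents do not support that; they support only that diagnostic status was not shown to be verified.

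The primary feasibility and acceptability results are not miscalculated, and no error rate is affected. The analytic consequence is confined to the exploratory clinical-significance categories, whose ceiling falls by k/n when k of n participants start below the cutoff. That consequence comes from how improvement is defined together with who is admitted, and does not depend on anyone being a non-case.

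**What to change.** 1. Reconcile Eligibility Criteria with Outcomes and Measures. If diagnostic criteria were ascertained by another method, state it in a sentence. If not, describe the sample in the report as women on an ED waitlist who screened positive. Recruitment has closed, so this means describing accurately what was done; the criterion should not be rewritten after the fact.
2. Do not present a diagnostic mix as confirmed. Summarise baseline EDE-Q severity and BMI for description only.
3. Report the clinical-significance categories for all participants as planned, and again with the denominator restricted to those above the clinical cutoff at baseline on the measure concerned. Give the number below the cutoff alongside.

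The cost is a slightly weaker sample description, a smaller denominator for the restricted summary, and one extra table from data already held. No new data collection is needed.

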### Intervention

MI-Coach is a self-help app created by Resiliens Inc [40] targeting motivation to engage in health behavior change (eg, exercising, smoking cessation, and sleep hygiene), and is widely available on both Apple and Android app stores. Developed in collaboration with a clinical psychologist and MI expert from the University of Queensland ([name]), the app features eight modules, consisting of over 35 lessons led by a registered clinical psychologist with accompanying exercises. In addition, the app includes short articles, mood and behavior assessments, mindfulness-based audio tracks, summary screens and analytics, community-based discussion groups, and the ability to communicate directly with a trained mental health professional.

For the purposes of this study, the content of MI-Coach was tailored for an ED population. In line with best practices for developing ED-specific digital interventions [17,30,41], an in-depth review of potentially iatrogenic or triggering content in the existing app was identified. Specifically, content referring to weight loss or health-focused exercise goals was identified, which prior research suggests may inadvertently reinforce disordered eating behaviors [28,30,37,42]. Subsequently, a literature review was conducted to identify MI topics and ED behavior change goals used in previous interventions, such as exploring reasons for and against pursuing treatment, validating the difficulties of addressing ED pathology, and identifying values and goals driving ED recovery efforts [11,17,30,41].

Following approaches outlined in previous research [15], the research team then performed iterative content analyses to remove or reframe any references misaligned with ED recovery principles (eg, shifting from weight-centric to motivation-centered goals that explore the individual’s reasons for seeking treatment, and the inclusion of topics such as ambivalence and identification of goals and values relevant to recovery). The overall structure and MI principles used in the original app were retained given their demonstrated effectiveness within an ED context [8]. Throughout this process, informal stakeholder consultations were conducted with ED-specialized clinicians involved in the project, who verified the appropriateness of the revised app content. All video lessons were subsequently refilmed using the University of British Columbia Okanagan’s recording studio and equipment. The new videos featured a clinical psychologist with ED treatment expertise to reduce discrepancies between the original and adapted app content (eg, clinical expertise and years of training). Examples of the MI-Coach: ED interface are provided in Figure 1.

Once the adaptation of app content was completed, a new section was built into the interface of the existing MI-Coach app by technological partners (Resiliens Inc) to house the adapted content. Several components of the base app (ie, assessments, audio tracks, analytics, discussion groups, and communication with the mental health professional) were removed to reduce the scope of the project and to protect participant confidentiality. The final adapted MI-Coach: ED app consisted of seven modules (Multimedia Appendix 2) targeting motivation to engage in ED recovery behaviors (eg, help-seeking, values exploration, and self-acceptance) covering the following topics sequentially: ambivalence and behavior change, self-acceptance and compassionate motivation, exploring possible behavior change goals, sustain and change talk, commitment language, and relapse prevention.

**Figure 1 figure1:**
[figure not shown]
Screenshots of the MI-Coach: ED interface illustrating (a) the home screen with session modules, (b) example module content, (c) brief videos, (d) examples of exercises available per module, and (e) example exercise content. Each feature targets ED-specific barriers such as ambivalence or low treatment motivation. ED: eating disorder.

### Outcomes and Measures

The primary outcomes that will be evaluated are the overall acceptability and feasibility of the MI-Coach: ED (Multimedia Appendix 3)*.* Feasibility will be assessed through attrition rates throughout the study period, frequency of app use, and module completion. Acceptability will be assessed through qualitative and quantitative feedback from participants through semistructured interviews and self-reports. Additionally, exploratory analyses will be conducted regarding the impacts of the MI-Coach: ED app on motivation and associated clinical characteristics.

Self-reported demographic data, including gender identity, age, level of education, ethnicity, and socioeconomic status were collected using Qualtrics, a web-based and secure data collection platform. Additionally, clinical data (ie, weight and height, history of ED treatment, age of ED onset, presence of cognitive difficulties, sensory deficits, history of traumatic brain injury, other mental health comorbidities, and ED waitlist experiences) was collected. The Sick, Control, One, Fat, and Food questionnaire [43], a brief screener that identifies the presence of common ED symptoms, was used to determine eligibility prior to enrollment. Clinical characteristics (ie, eating pathology, recovery motivation, body dissatisfaction, depression, and anxiety symptoms) were evaluated through several self-report questionnaires administered at baseline and posttest, including the Eating Disorder Examination Questionnaire (EDE-Q) [44], the Readiness and Motivation for Change Questionnaire (RMQ) [45], the Body Shape Questionnaire (BSQ) [46], the Patient Health Questionnaire-9 (PHQ-9) [47], and the 7-item General Anxiety Disorder Scale (GAD-7) [48]. Additionally, technological literacy was evaluated at baseline using the Mobile Device Proficiency Questionnaire [49] and the eHealth Literacy Scale [50].

Quantitative measures of feasibility and acceptability of the MI-Coach: ED app were assessed using an adapted version of the TAM Questionnaire [31] and the user version of the Mobile App Rating Scale (uMARS) [51]. The adapted version of the TAM questionnaire includes changes to each item to better fit the research question and sample characteristics of this study (eg, “Using CHART-MASTER in my job would enable me to accomplish tasks more quickly” was modified to “Using MI-Coach: ED allowed me to access mental health services more quickly”). An optional semistructured interview was conducted with interested participants to assess their experiences with the app and to further evaluate the feasibility and acceptability of MI-Coach: ED.

An overview of participant flow is provided in Figure 2. Participants were recruited between November 2022 and April 2024. Clinicians and administrators working in a range of ED treatment settings (eg, provincial health authorities, nonprofit charities, and private practice clinics) were contacted via email and asked to share the recruitment advertisement with clients on their waitlists. Interested participants were asked to communicate with the study team via email to enroll in the study. Once initial contact was established, a 15-minute telephone screener was conducted by the study team to assess participants’ eligibility for the study and to provide additional details regarding the study. The Sick, Control, One, Fat, and Food questionnaire was used to evaluate the presence of ED symptoms. Once eligibility was established, consent (Multimedia Appendix 4) and baseline measures were collected through Qualtrics, including a demographics questionnaire, the EDE-Q, the RMQ, the PHQ-9, the GAD-7, and the BSQ. Following this, an onboarding session was conducted through a secure videoconferencing platform (ie, Zoom), during which participants were given a demonstration on downloading and using the app and provided their log-in information.

The subsequent pilot-test portion of the study consisted of a four-week period during which participants used the app in a naturalistic way. Following study completion, participants were compensated CAD $10 (≈US $7.10) for each study portion completed (ie, baseline questionnaire package, onboarding session, posttest questionnaire package, and exit interview), receiving up to CAD $40 (≈US $28.41) through the Tango Card rewards platform. To reduce the impact of possible confounds (eg, financial motivation), participants were informed that their compensation would not be impacted by their app use during the pilot test phase and that there are no minimum requirements for app use. Once the pilot test was completed, a second brief consent form (Multimedia Appendix 5) and posttest questionnaires assessing self-reported clinical features (ie, the EDE-Q, RMQ, PHQ-9, GAD-7, and BSQ) and feedback regarding the app (ie, the adapted TAM-Q and uMARS) were completed. Finally, participants were invited to participate in a videoconferencing-based exit interview to provide additional feedback on their experience with the study author. The semistructured interview guide (Multimedia Appendix 6) was used as an outline to standardize the interview process across participants [52].

